#### Control group

Participants in the control group will be on a waiting list for the first 6 months of the study and will receive the self-help book after they complete the 6-month follow-up assessment. For the sake of comparison at the long-term follow-up, the control group will also receive the information emails in the same way provided in the TL-I group.

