### Sample Size

Well-being is the primary outcome used for the power calculation. We expect to detect a significant effect on well-being between the experimental groups TL-E and TL-I compared to the WL group. Based on recent meta-analyses [17,18] and a previous comparable study [38], we expect to find a standardized effect size on well-being of 0.40 or larger. The targeted sample size is 99 participants per group (297 in total) to provide a statistical power of (1 - *β*) = 80% and a 5% significance level (two-tailed). To allow a study dropout rate of 25%, we need 132 participants in each condition and 396 participants in total for the trial.

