### Statistical Analyses

The Consolidated Standards of Reporting Trials (CONSORT) statement [91] will be used to report the results. Independent *t* tests and Chi-square statistics (X^2^) will be used to examine baseline differences between the study groups. Non-significant socio-demographic differences at baseline will indicate successful randomization. Internal consistency of the constructs will be determined using Cronbach’s alpha. To examine the efficacy of the intervention, intention-to-treat analyses will be conducted by including all participants in the analyses who have been randomized. The Expectation Maximization (EM) method will be used to impute all missing data on the continuous measures of T1, T2 and T3. This method imputes the data by maximum likelihood estimation using the observed data in an iterative process [92]. The intention-to-treat analysis will be compared with a completers-only analysis.

To examine significant differences between the 3 groups, we will perform repeated measures ANOVA in a 3 (group) x 3 (time) design with well-being (MHC-SF and FS) as the primary dependent variable and positive/negative emotions (mDES), the use of strengths (SUS), optimism (LOT-R), self-compassion (SCS-SF), resilience (BRS), and positive relations with others (SPR) as the secondary dependent variables. Significant time x group interactions will be tested with Tukey’ post hoc tests. Within-group effects (Cohen’s *d*) will be calculated by subtracting the mean post-test or follow-up score from the mean baseline score and dividing the difference by the pooled standard deviation. Between-group effects (Cohen’s *d*) will be calculated by subtracting the mean post-test or follow-up score of the experimental group from the mean post-test or follow-up score of the control group, and dividing the difference by the pooled standard deviation [93]. These effect sizes are used to gain insight into the relevance of the significant effects. To examine changes in the amount of flourishers, languishers, and moderately mentally healthy (MHC-SF), descriptive statistics will be used. Changes in categories will be tested with X^2^-statistics.

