There could be several limitations that need to be considered in advance. First, our results might not be generalizable to the general Dutch population, since we will use a self-selected sample and apply exclusion criteria on the level of well-being and clinical symptomatology. It is not unlikely that our open recruitment with advertisement in national newspapers will attract mostly highly-educated women. However, we will use a randomization procedure stratified by gender and education, which will create equal distribution of these characteristics to each group and therefore not harm the internal validity of our study. Second, non-adherence to the intervention and drop out from assessments (incomplete data) could occur. Both types of attrition are closely related and may bias our results [98]. Reasons for non-adherence and dropout could be related to individual characteristics (ie, low-educated individuals might find the intervention and/or assessments too difficult), characteristics of the intervention (ie, individuals in the experimental conditions receive the self-help book after baseline and are unaware of the content of the book and type of exercises when they apply for the study), and characteristics of the study (ie, participants will be given instructions and a time schedule) [98]. To gain insight on adherence in our study, participants will be asked about time spent on each module, and the personal counselors will gather reasons for non-adherence mentioned in the email correspondence. Although we expect to find higher adherence rates for individuals in the TL-E condition than has previously been found for Web-based multicomponent PPIs [24,25,27], it could be lower than in face-to-face multicomponent PPIs [20,22,23]. However, our study can only draw conclusions about the comparison of the self-help book with email support to the self-help book without email support. Differences in adherence and efficacy between face-to-face support, email support, and no support warrant attention in future research. Furthermore, to prevent low power due to drop out, we have taken into account an attrition rate of 25% in our power analysis. We will also conduct dropout analysis to identify any selectiveness or characteristics of attrition that may be relevant for real-life implementation of the intervention. Third, the use of senior positive psychology students for the email support can be a risk for the professionalism of our intervention because these students are unexperienced psychologists. We will try to reduce this risk by providing extensive supervision from experienced psychologists and by only selecting students who are thoroughly trained in email support and who have practiced the self-help book. On the other hand, the guidance is primarily process-oriented and advanced clinical counseling skills are therefore not considered necessary. The benefit of using students as counselors is that the intervention costs will be very low. If proven effective, it could be even more effective when implemented in a mental health service with experienced and professional counselors, although this could be disadvantageous for its cost-effectivity. Nevertheless, this needs to be tested in future research.

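### Neither planned check on missing data can show whether dropouts did worse than their observed data predict, a bias the protocol itself warns of

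*Protocol article*

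**What the plan says.** The Statistical Analyses section of the protocol article defines the intention-to-treat analysis as including everyone randomised. All missing continuous outcomes at T1, T2 and T3 are filled in by EM, which the section describes as maximum likelihood estimation from the observed data. The stated comparison is: "The intention-to-treat analysis will be compared with a completers-only analysis".

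The Discussion treats non-adherence and incomplete assessments as things that could occur, and says: "Both types of attrition are closely related and may bias our results". It then plans a dropout analysis to see whether attrition is selective, with real-life implementation as the reason given. It also has counselors note reasons for non-adherence found in the email correspondence.

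The Sample Size section allows for attrition: "To allow a study dropout rate of 25%, we need 132 participants in each condition and 396 participants in total for the trial".

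The Control group section says that waiting-list participants "will receive the self-help book after they complete the 6-month follow-up assessment".

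**The concern.** The EM analysis predicts each missing score from observed participants with similar recorded data. The completers-only analysis leaves the dropouts out. Neither allows for dropouts who did worse than their recorded data would suggest. If people in the book arms stop answering because they stopped using the book, that is the departure that matters.

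The recorded data may not be enough for EM to correct this. According to Table 2, invested time and adherence in the book arms are collected at T1, so someone who misses T1 will usually have no adherence record either. TL-I participants are told not to reply to the weekly emails, so no correspondence fills the gap. In TL-E the counselors do hold some information, but the analysis section does not bring it into the imputation.

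At stake is the estimated effect of offering the book, which the authors want public mental health services and governments to use. Agreement between the two analyses could be read as showing that dropout did no harm, when it would not show that.

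**Working it through.** **1. The plan's own figures.** The inputs from Sample Size are "we expect to find a standardized effect size on well-being of 0.40 or larger", 80% power, 5% two-sided, and "The targeted sample size is 99 participants per group (297 in total". The two-mean formula with d = 0.40 gives 99 per group (power 0.804 by the normal approximation, 0.800 by the exact t test). Inflation for dropout: 99 / (1 − 0.25) = 132, and 3 × 132 = 396. All figures reproduce, and the point does not depend on any error in them.

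**2. Effect over all randomised if dropouts gain less.** Let e be the effect in book-arm completers, p the share of the book arm that drops out, and g the fraction of the benefit that dropouts obtain. Assume waiting-list dropouts resemble waiting-list completers.

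Effect over all randomised = e(1 − p) + e·g·p

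The values e = 0.40 and p = 0.25 are the plan's. The other values of p, and both values of g, are assumptions.

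| p | g = 0 | g = 0.5 |
|---|---|---|
| 0.25 | 0.40 × 0.75 = 0.30 | 0.30 + 0.20 × 0.25 = 0.35 |
| 0.35 | 0.40 × 0.65 = 0.26 | 0.26 + 0.20 × 0.35 = 0.33 |
| 0.40 | 0.40 × 0.60 = 0.24 | 0.24 + 0.20 × 0.40 = 0.32 |

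**3. Would the two planned analyses reveal it?** This step works from the other end and fixes the true effect over all randomised at 0.40. Assume that only adherers benefit, that 25% of the book arm drops out and all of these are non-adherers, that 25% of the waiting list drops out at random, and that EM is run within arm. If the dropouts give no post-baseline data, the completers' effect is 0.40 / (1 − 0.25) = 0.53. Baseline scores do not separate adherers from non-adherers here, so EM gives the same. A large simulation with baseline-outcome correlation 0.6 and 50–75% adherers gave 0.53–0.54 from both analyses, which agreed to within 0.003. With 40% dropout in the book arm, 0.40 / (1 − 0.40) = 0.67, and both again gave about 0.67.

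**4. When dropouts do give T1 data.** The same set-up was carried to T2 with 60% adherers and all correlations 0.6. The true effect is 0.40 throughout.

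| When dropouts leave | EM at T2 | Completers-only at T2 |
|---|---|---|
| All before T1 | 0.53 | 0.53 |
| Half before T1 | 0.50 | 0.53 |
| All after T1 | 0.47–0.48 | 0.53 |

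Once T1 scores are recorded, EM uses them. Part of the bias goes, and the two analyses begin to differ.

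**5. Direction.** With 25% random dropout and EM run on both arms pooled without group in the model, a true 0.40 became 0.30. The article does not say whether group is in the EM model.

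**6. What a delta analysis would show.** Suppose the imputed effect is 0.40 with 25% of the book arm missing, and those participants truly score s SD below their imputed values. The effect is then 0.40 − 0.25s. For s = 0, 0.2, 0.4, 0.6 and 0.8 (an assumed range) it is 0.40, 0.35, 0.30, 0.25 and 0.20.

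**The case against.** The strongest objection is that this is a condensed article and that sensitivity analyses for departures from missing at random usually sit in the statistical analysis plan, which is not shown. That plan may well contain more. The point stands because it concerns what the article does state: it names a check and names a bias, and the check cannot address that bias.

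Several stronger readings are tempting, and the protocol does not support them.

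- *The completers-only comparison is the only safeguard.* It is not. The Discussion also plans a dropout analysis and the collection of reasons for non-adherence. These can show selectiveness on measured characteristics. They cannot show how unseen outcomes differ, and they do not alter the estimate.
- *The protocol expects biased dropout.* It says attrition could occur and may bias the results. The 25% is a planning allowance with no link to adherence or arm.
- *The comparison never tells anything.* Step 4 shows that EM and completers-only can diverge at T2 when dropouts have T1 data. If book-arm dropout depends on a low T1 score alone, a simulation under the same kind of assumptions had EM recover 0.40 while completers-only gave 0.69.
- *The effect will be overstated.* Step 5 gives an understatement under another reading of the EM model.
- *Retention will differ by arm because the waiting list must finish T2 to receive the book.* That incentive makes a difference plausible, but no retention figures by arm are given.

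**Conclusion.** The point holds in a limited form. The completers-only comparison and the dropout analysis cannot test whether dropouts did worse than their observed data predict, although the protocol warns that dropout tied to non-adherence may bias its results. The gap is greatest for participants with no post-baseline data, because the two analyses then agree whether or not both misstate the effect.

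The sizes are illustrative. A fall from 0.40 to 0.30 SD needs the planned 25% dropout and no gain at all in dropouts, which is the extreme case; with half the gain it is 0.35. Dropout of 35% or 40% appears nowhere in the protocol. Direction and size depend on who drops out in each arm, on whether they answer T1, and on whether group is in the EM model. This uncertainty is a reason to vary the assumption by arm instead of relying on agreement between two analyses of the same observed data.

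**What to change.** Keep the completers-only analysis and label it descriptive. For the T1 and T2 contrasts of TL-E and TL-I with the waiting list, add a sensitivity analysis by multiple imputation with group in the imputation model and a delta adjustment set separately for each arm. Include as one scenario reference-based imputation, in which book-arm dropouts follow the waiting-list trajectory. This is one assumption among several and should not be presented as the correct answer. Report the shift at which the conclusion changes, so that readers can judge whether so large a shortfall in dropouts is credible.

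No new data, participants or visits are needed. The cost is a little more analysis work and a sensitivity estimate that may be less favourable than the main one.

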### Randomization

Randomization will be conducted after all eligible participants complete the baseline questionnaire, with 396 participants being randomly assigned to 1 of the 3 groups (allocation ratio, 1:1:1). Randomization will be stratified by gender and educational level (ie, low, medium, high) using a computerized random number generator created with Excel. This is an automated process with no interference from the investigators.

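### The primary 3 x 3 repeated measures ANOVA adjusts for neither baseline nor the strata and leaves the Tukey contrasts at T1 and T2 undefined, which costs precision on the pairwise comparisons

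*Protocol article*

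**What the plan says.** All of the following is in the protocol article.

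- **Model (Statistical Analyses).** For MHC-SF and FS, and for the component scales, "we will perform repeated measures ANOVA in a 3 (group) x 3 (time) design". No covariate is named, and the three times are not listed. Significant time-by-group interactions are followed by Tukey post hoc tests.
- **Strata (Randomization).** "Randomization will be stratified by gender and educational level (ie, low, medium, high"). In the analysis, gender and education return only as moderators.
- **Hypotheses (This Study).** TL-E is expected to be equivalent or superior to TL-I and superior to WL at post-test and 6 months, and both book arms are to be compared with WL.
- **Between-group effect size (Statistical Analyses).** Cohen's d takes the experimental arm's mean away from the control arm's mean at the same time point, over the pooled SD. The within-group d subtracts the later mean from the baseline mean.
- **Baseline check (Statistical Analyses).** "Non-significant socio-demographic differences at baseline will indicate successful randomization".
- **Sample size.** On the effect, "we expect to find a standardized effect size on well-being of 0.40 or larger". On numbers before attrition, "The targeted sample size is 99 participants per group (297 in total"), and after it, "To allow a study dropout rate of 25%, we need 132 participants in each condition and 396 participants in total".

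**The concern.** The hypotheses concern arm differences at two named times. An omnibus interaction with 4 degrees of freedom shows only that the profiles differ somewhere. Tukey's procedure compares group means, so the text must say which means: raw scores at each time, changes from T0, or the group factor averaged over all times. These choices differ in target and in precision.

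With T0 as a response level, the interaction rests on changes from baseline. Those are never more precise than a baseline-adjusted comparison, and at low correlation they are much less precise. T0 scores and strata are held for every randomized participant, so the precision costs nothing to recover.

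Two smaller points sit in the same section. The between-group d, as defined, is negative when the book helps, although the planned effect is +0.40. And the baseline rule treats significance tests as evidence on whether randomization worked, which they cannot supply.

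**Working it through.** **1. The plan's own figure.** Inputs from Sample Size: d = 0.40, "80% and a 5% significance level (two-tailed"). n = 2(1.960 + 0.842)² / 0.40² = 98.1, so 99 per arm. 99 / 0.75 = 132, and 3 × 132 = 396. The stated figures reproduce. They fit an unadjusted two-group comparison of raw scores, not the interaction or a Tukey test.

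**2. Which three times.** There are four assessments. WL participants receive the book after the 6-month assessment (Control group). The component scales, analysed in the same design, are not collected from controls at T3 (Table 2, note d). T0, T1, T2 is therefore the only set that works for all listed outcomes. This is an inference; the article does not state it.

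**3. Assumptions.** SD 1 and equal correlation ρ between all times. The documents give no ρ, so 0.3 to 0.7 is shown. n = 99 per arm; true effect 0.40 in both book arms at T1 and T2.

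**4. Power of the planned interaction test.** Centred over time, a book arm's profile (0, 0.4, 0.4) is (−0.267, 0.133, 0.133), with sum of squares 0.1067. Across three arms the interaction sum of squares is (4/9 + 1/9 + 1/9) × 0.1067 = 0.0711 per participant per arm. Noncentrality = 99 × 0.0711 / (1 − ρ) = 7.04 / (1 − ρ), which is 10.1, 14.1 and 23.5 at ρ = 0.3, 0.5 and 0.7. On 4 and 588 df, power is about 72%, 87% and 98%. A simulation of 3,000 runs gave 72%, 86% and 98%.

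**5. Power of one pairwise contrast at one time.** The standard error is √(2V/99), where V = 1 for raw scores, 2(1 − ρ) for change and 1 − ρ² for baseline adjustment. The Tukey critical value on the t scale (3 groups, 294 df) is 2.356.

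| ρ | Adjusted | Change | Raw | V adjusted / V change = (1 + ρ)/2 |
|---|---|---|---|---|
| 0.3 | 72% | 51% | 68% | 0.65 |
| 0.5 | 81% | 68% | 68% | 0.75 |
| 0.7 | 94% | 90% | 68% | 0.85 |

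On the plan's own footing (unadjusted 5%, 80% power), change scores need 138, 99 and 59 per arm. Baseline adjustment needs 90, 74 and 51.

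**6. If Tukey were run on the group factor.** The difference averaged over T0, T1 and T2 is (0 + 0.4 + 0.4)/3 = 0.267, with variance (1 + 2ρ)/3. Tukey power is then 58%, 48% and 40%.

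**7. Strata.** If gender and education explain an assumed 1% to 5% of residual variance, the adjusted requirement at ρ = 0.5 falls from 74 to between 73 and 70 per arm.

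**8. Sign of d.** Subtracting the experimental mean from the control mean gives control minus experimental. A true benefit of 0.40 is reported as −0.40. The within-group d, baseline minus follow-up, is reversed in the same way.

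**9. Baseline rule.** Seven sociodemographic variables are listed in Table 2, and two of them (gender and education) are stratified. For the other five, one independent test each, 1 − 0.95⁵ = 0.23: perfect randomization yields at least one p < 0.05 in about 23% of trials.

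**The case against.** The strongest reply is that randomization keeps the planned interaction test valid, and that its power is 87% or more for ρ of 0.5 or above. That stands. A reader might infer that the primary test is invalid or generally underpowered; the calculation does not support that. It falls below 80% only at the lower correlations.

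A reader might also take the 40% to 58% in step 6 as the plan's power. Those figures need one reading of an ambiguous sentence, and comparing arms at each time is equally natural. The documents support only that the follow-up contrasts are undefined.

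Nor can it be said that the stated contrasts go unestimated: d against control is planned at post-test and follow-up, and under randomization the raw difference targets the same mean effect as the adjusted one. What is missing is a defined test, baseline adjustment, and a d for TL-E versus TL-I.

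Three further replies carry weight. A condensed article may leave covariates to a fuller plan, and the strata gain is small. No analysis depends on the sign of d or on the baseline rule, so both are matters of wording. And with three pairwise comparisons of interest, an omnibus test followed by all-pairs Tukey is sensible in structure, so any replacement must keep multiplicity control. None of this answers the precision loss on the pairwise contrasts: the model is named, and it is less efficient than one the same data allow.

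**Conclusion.** The point holds as an efficiency and specification defect, not as a validity failure. On the T0, T1, T2 reading, moving from change scores to baseline adjustment cuts the variance of a pairwise contrast by 35%, 25% and 15% at ρ = 0.3, 0.5 and 0.7. It raises Tukey-adjusted power at one time by about 21, 14 and 4 percentage points. Against raw scores, the gain runs from about 5 points at ρ = 0.3 to 27 at 0.7. These figures rest on assumed correlations, equal correlation between times, 99 analysed per arm and a true effect of 0.40.

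The sample size need not rise. The stated 80% refers to an unadjusted 5% comparison, and on that footing baseline adjustment gives 84%, 90% and 98% with 99 per arm. Under Tukey, adjusted power at ρ = 0.3 is still 72%, so adjustment does not guarantee 80% for each pairwise test at low correlation. The sign of d and the baseline rule are minor but should be corrected.

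**What to change.** 1. Name the three time points of the primary analysis.
2. Replace the ANOVA with a mixed model of the T1 and T2 scores containing arm, time, arm × time, T0 score × time, gender and education.
3. Test TL-E versus WL, TL-I versus WL and TL-E versus TL-I at T1 and at T2, with Tukey or equivalent multiplicity control, and report adjusted differences with 95% confidence intervals.
4. Define between-group d as experimental minus control and within-group d as follow-up minus baseline, so that benefit on well-being is positive, as in the planned 0.40.
5. Delete the rule linking non-significant baseline differences to successful randomization, and tabulate baseline characteristics by arm.

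The cost is analysis wording only. Baseline scores and strata are already collected, and neither recruitment nor the assessment schedule changes.

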Adults aged 18 or above with low or moderate levels of well-being without moderate or severe clinical symptomatology are eligible for this study because previous studies have shown that these individuals might search for happiness [41] and could boost their mental health by elevating the level of well-being [7,8]. Other inclusion criteria are a sufficient internet connection, a valid email address, and a willingness to invest an average of 4 hours per week for 8-12 weeks. In the screening questionnaire, the Mental Health Continuum Short Form (MHC-SF) will be used to assess the level of well-being and the Hospital Anxiety and Depression Scale (HADS) will be used to assess the level of clinical symptomatology. Participants will be excluded from the study if they score 4 or 5 (range 0-5) on at least 1 of the 3 emotional well-being items in combination with a score of 4 or 5 (range 0-5) on at least 6 of the 11 social and psychological well-being items of the MHC-SF, which is operationalized as flourishing (ie, high levels of well-being) [13,43]. Participants will also be excluded if they score 10 or higher (range 0-21) on the depression scale and/or on the anxiety scale of the HADS, which indicates individuals with moderate or severe clinical symptomatology [44]. Participants who will be excluded from the study will be notified by email because, (1) they are already flourishing, or (2) they probably have at least moderate depression or anxiety symptoms. The latter group will receive their specific scores and their meaning on the HADS and will be advised to talk to their general practitioner when symptoms persist or increase. After screening, the remaining participants receive a personal email link to the baseline questionnaire.

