### Measures

For a brief overview of all outcome measures and assessment times, see Table 2. Because one of our aims is to examine the working mechanisms underlying the intervention, which requires assessing all included positive psychology components, measures are selected on brevity and availability in the Dutch language.

**Table 2 table2:** Intended questionnaires and assessment times.

			T0	T1	T2	T3
Questionnaire	Measurement	Screening	Pre-test	Post-test	Follow-up^a^	Follow-up^b^
MHC-SF	Well-being/ flourishing	X	X	X	X	X
FS	Social-psychological well-being		X	X	X	X
HADS	Symptoms of depression and anxiety	X			X	X
m-DES	Positive and negative emotions		X	X	X	X^d^
SUS	Use of strengths		X	X	X	X^d^
LOT-R	Optimism		X	X	X	X^d^
SCS-SF	Self-compassion		X	X	X	X^d^
BRS	Resilience		X	X	X	X^d^
SPR	Positive relations		X	X	X	X^d^
EPQ-RSS	Extraversion and neuroticism		X			
NEO-FFI	Conscientiousness		X			
MCQ	Direct medical consumption costs		X	X^c^	X^c^	X
PCQ	Non-medical productivity costs		X			X
Brugha Life-events	Positive and negative life-events		X	X	X	X
CSQ-8	Client satisfaction			X^d^		
Process evaluation	Invested time, adherence, positive changes			X^d^		X^e^
	Level of (continued) use					X
Demographics	Gender, age, education, marital status, living situation, ethnicity, daily activities	X				

^a^ 6 months after T0.

^b^ 12 months after T0.

^c^ Only medical health care costs are assessed, not medication costs.

^d^ Only assessed in the experimental groups, not the control group.

^e^ Only assessed in the control group, not the experimental groups.

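### Two MHC-SF scores are taken before randomisation, but the planned efficacy ANOVA uses at most one, so some precision on the MHC-SF is given up; the analysis stays valid.

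*Protocol article*

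**What the plan says.** All references are to the Protocol article.

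- **Participants:** "In the screening questionnaire, the Mental Health Continuum Short Form (MHC-SF) will be used to assess the level of well-being", with the HADS alongside it. People who pass are then sent a separate link to the baseline questionnaire.
- **Measures, Table 2:** the MHC-SF row, labelled "Well-being/ flourishing", is marked at screening, T0, T1, T2 and T3. The FS is marked from T0 onward but not at screening. The HADS is marked at screening, T2 and T3.
- **Randomization:** "Randomization will be conducted after all eligible participants complete the baseline questionnaire". Both the screening and the T0 scores therefore precede allocation.
- **Statistical Analyses:** a 3 x 3 repeated measures ANOVA "with well-being (MHC-SF and FS) as the primary dependent variable", followed by Tukey post hoc tests. No covariate is named. The within-group effect sizes use the baseline mean, and the moderator list does not contain the screening scores.
- **Sample Size:** "we expect to find a standardized effect size on well-being of 0.40 or larger", with 80% power at a two-sided 5% level, giving 99 per group. Then: "To allow a study dropout rate of 25%, we need 132 participants in each condition and 396 participants in total".

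**The concern.** A single T0 score is a noisy measure of a person's usual well-being. A second score on the same scale, also taken before allocation, removes part of that noise from every comparison between arms at no cost in data. The time factor has three levels and the MHC-SF is taken on five occasions, so the model cannot hold them all. The article does not list the three. T0, T1 and T2 is the natural reading, because the control group receives the book after the 6-month assessment. On that reading T0 is the only pre-treatment score in the model.

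At stake are the standard errors of the three pairwise MHC-SF contrasts. The sample size was set for each experimental arm against the waiting list. The comparison of the two book arms is likely to be smaller than that target, so precision matters most there.

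**Working it through.** **1. The plan's own figure.** Inputs from Sample Size: d = 0.40, two-sided alpha 0.05, power 80%, dropout 25%.
n = 2 x (1.960 + 0.842)^2 / 0.40^2 = 98.1, rounded up to 99 per group. 99 / 0.75 = 132 per group, and 3 x 132 = 396. The stated figures reproduce. They are those of an unadjusted two-group comparison, so the stated power does not depend on any covariate.

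**2. Residual variance with one and with two pre-scores.** Scale the MHC-SF to variance 1. Let r be the correlation of each pre-score with a later score, and s the correlation of screening with T0. The article gives neither, so all values below are assumptions.
- Adjusting for T0 only: 1 - r^2
- Adjusting for T0 and screening: 1 - 2r^2/(1 + s)

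| r | s | T0 only | T0 + screening | Reduction |
|---|---|---|---|---|
| 0.5 | 0.5 | 0.750 | 0.667 | 11.1% |
| 0.6 | 0.6 | 0.640 | 0.550 | 14.1% |
| 0.7 | 0.7 | 0.510 | 0.424 | 17.0% |
| 0.5 | 0.8 | 0.750 | 0.722 | 3.7% |
| 0.7 | 0.8 | 0.510 | 0.456 | 10.7% |

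**3. Allowing for the eligibility rule.** Flourishers are excluded at screening, which narrows the range of the screening score. This was approximated by simulating trivariate normal scores and removing the top 20% (assumed) or 37% (the Dutch flourishing rate in the Introduction). Reductions beyond T0 adjustment:
- Equal correlations (r = s) from 0.6 to 0.8: about 8% to 17%.
- r = 0.6, s = 0.8: 4.4% to 5.1%.
- r = 0.6, s = 0.85: 3.4% to 3.9%.
- r = 0.5, s = 0.8: 2.6% to 2.9%.
- T0 correlating 0.60 and screening 0.57 with the later score, s = 0.85: 1.5% to 1.7%.
- r = 0.7, s = 0.8, top 37% removed: 7.6%. A high s therefore does not always make the gain negligible.

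The HADS exclusion may also trim the low end. If it removed the bottom 20% of screening scores as well (assumed), the case r = 0.6, s = 0.8 falls to 1.7% to 2.8%.

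**4. Adding screening to the ANOVA as planned.** With T0 as an outcome level, the treatment contrast rests on change from T0, which has variance 2(1 - r). The covariance of that change with screening is r - s, so the proportional gain is (r - s)^2 / [2(1 - r)].
- r = s: exactly 0.
- r = 0.6, s = 0.8, before truncation: 0.04 / 0.80 = 5%.

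Across the truncated cases the gain is 0% to 6%. The gains in steps 2 and 3 need both scores on the covariate side.

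**5. Averaging the two scores.** If both correlate equally with the outcome, the best weights are equal and the average does as well as two terms. If not, the average imposes the wrong weights. With correlations 0.60 (T0), 0.57 (screening) and s = 0.85, the best weights are (0.60 - 0.85 x 0.57)/(1 - 0.85^2) = 0.42 for T0 and (0.57 - 0.85 x 0.60)/(1 - 0.85^2) = 0.22 for screening. Separate terms are never worse in residual variance.

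**6. What belongs to this point.** With r = s = 0.6, change from T0 has variance 0.80, T0 adjustment gives 0.64, and T0 plus screening gives 0.55. The step from 0.80 to 0.64 concerns how T0 is handled. Only the step from 0.64 to 0.55 is credited to the screening score.

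**The case against.** - **Nothing is wrong in the strict sense.** Using screening as an eligibility filter and T0 as baseline is ordinary practice. The ANOVA is not biased by leaving the screening score out, and the sample size reproduces. This stands, and it limits the point to efficiency. A reader might infer that the planned analysis is invalid or the trial underpowered for this reason; the documents support neither.
- **Covariates may be left to an analysis plan that is not shown.** A fuller document could add the term, and the predictors for the EM imputation are also unlisted. But the article does fix the model, its factors and its post hoc test, and that model has no place for the screening score. Using the score in imputation would not adjust the contrasts between arms.
- **The size rests on unseen correlations.** This stands. The larger figures assume that screening correlates with T0 no more strongly than T0 does with a score about 3 months later. T0 follows screening with no intervention between them, so a higher s is at least as plausible, and several such cases fall below 4%. The flourishing rule is also an item pattern, which a percentile cut only approximates.
- **The comparator is a T0-adjusted model, which is not the planned one.** This is also correct, and it is why the fix must move T0 to the covariate side as well.

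**Conclusion.** The point holds as a modest loss of efficiency. Two pre-randomisation MHC-SF scores exist for every randomised participant, and the planned model uses at most one. Beyond T0 adjustment, the screening score would lower residual variance by about 1.5% to 17%. The upper part of that range needs equal correlations across occasions; the lower part applies if screening and T0 correlate at about 0.8 to 0.85 and later scores less strongly. Every figure rests on assumed correlations and on an approximate treatment of the eligibility cut.

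Two stronger readings are tempting. A reader might convert the gain into a number of participants saved out of 396. The documents give no correlations and no interval between screening and T0, so no such count can be supported. A reader might also extend the gain to the FS or add a further gain from the HADS. The FS has no screening score, and neither gain has been quantified.

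**What to change.** In Statistical Analyses, specify that the post-baseline MHC-SF scores (T1 and T2 on the natural reading of the three time levels) are the outcomes, with T0 MHC-SF and screening MHC-SF as two separate covariates, named before the data are analysed. Do not average the two scores, and do not merely add screening to an ANOVA in which T0 remains an outcome level. If the authors prefer to keep the planned model, one sentence saying why the screening score is not used would suffice. Using the screening MHC-SF in the FS model, or the screening HADS in either model, can be left optional with no gain claimed.

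The cost is a restated model with one covariate beyond T0. The screening score is needed for eligibility, so it is already held for everyone randomised, and it precedes allocation, so it introduces no bias. No visits, questionnaires or participants are added, and the sample size statement need not change.
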